## Abstract

**Background/Objectives:** Endovascular aneurysm repair (EVAR) of the aorta may trigger an inflammatory response that affects coagulation. In the EVAR of para-renal and thoraco-abdominal aortic aneurysms, the implants are more complex and the duration of surgery is longer. However, the exact pathophysiological mechanisms of coagulation activation are not yet well understood. The primary aim of this study is to investigate the effects of complex EVAR of para-renal and thoraco-abdominal aortic aneurysms on the coagulation status of patients. **Methods:** This prospective observational study (STROBE), approved and registered by the Ethics Committee of the University Hospital of Larissa (UHL) (NCT06432387), will enroll consecutive patients undergoing elective EVAR of para-renal and thoraco-abdominal aortic aneurysms. Exclusion criteria: Refusal to participate, previous surgery within 3 months, American Society of Anesthesiologists physical status (ASA PS) > 3, known history of thrombophilia or functional platelet dysfunction. Perioperative laboratory tests will be performed according to institutional guidelines. These include a complete blood count, conventional coagulation tests, and kidney and liver function tests. In addition, the following parameters will be determined: von Willebrand factor, factors VIII and XI, D-dimers, fibrinogen, Adamts-13, anti-Xa, platelet activation (multiplate), and high-sensitivity troponin. Blood samples will be taken pre-operatively before induction of anesthesia (01), on postoperative day 1 (02), and on postoperative day 3–4 (03). During hospitalization, myocardial injury after non-cardiac surgery (MINS), major adverse cardiovascular events after non-cardiac surgery (MACE), acute kidney injury (AKI), post-implantation syndrome (PIS), and death from any cause will be recorded. In addition, our patients will be reviewed at 30 days, 3, 6, and 12 months for MACE, implant failure, or death from any cause. All enrolled patients will be treated by the same medical team at UHL according to the indications. According to our power analysis, for a cohort of patients with three consecutive measurements, 58 patients should be included in the study. To compensate for possible dropouts, the sample size was increased to 65 patients. **Conclusions:** The results of the present study could help physicians to better understand the effects of complex EVAR of para-renal and thoraco-abdominal aortic aneurysms on blood coagulation and platelet activation.

## 1. Introduction

### 1.1. Background and Rationale

The development of endovascular techniques in recent decades has changed the treatment of aortic aneurysms [1]. For patients with complex aortic disease, including pararenal abdominal aortic aneurysms (PRAAA) and thoraco-abdominal aortic aneurysms (TAAA), complex endovascular aneurysm repair (EVAR) with the fenestrated or branched EVAR technique (F/BEVAR) was introduced as early as 2012 [1,2,3]. Complex EVAR enables the safe minimally invasive treatment of complex aortic disease in patients with appropriate anatomy and perioperative risk [2,3].

Compared to traditional open surgery (OS), EVAR is characterized by a more favorable short-term outcome in terms of mortality and morbidity in high-risk patients [1,4]. However, despite this, EVAR and thoracic EVAR (TEVAR) appear to be associated with a prominent prothrombotic coagulopathy according to several reports [4,5,6,7,8]. It should be highlighted that the pro-coagulant activity of EVAR and TEVAR is greater when compared with open procedures, and it may lead to higher morbidity due to micro- and macro-vascular thrombosis [5,6,9].

Over the years, EVAR has been associated with increased platelet consumption, increased thrombin activity, increased thrombin generation, and increased fibrinolysis [10]. On the other hand, TEVAR has been associated with increased postoperative platelet consumption and elongation of prothrombin time [6]. Moreover, in contrast to open aneurysm repair (where the aortic thrombus is removed), it has been suggested that the resultant coagulopathy may persist for several months after endovascular procedures, and this may contribute to the development of an aortic thrombus [11].

As far as platelet alterations are concerned, the presence of an abdominal aortic aneurysm (AAA) along the endovascular procedure exhibits a strong impact on platelets [8]. AAA leads to a chronic pro-inflammatory response, which is characterized by increased platelet activation and decreased platelet count [8]. The post-inflammatory response following EVAR exaggerates the decrease in platelet count; however, there are still controversies regarding its impact on platelet activity [8]. Of note, there is a paucity of data regarding the impact of complex EVAR on platelets.

Intraoperative injury to the vascular endothelium, the use of endovascular tools, the mechanical manipulation of the intramural thrombus of the aneurysm during stent–graft implantation, the manipulation of guidewires and catheters in the vessels, the activation of platelets by the graft material, and the use of contrast media have all been recognized as the possible contributing factors of coagulation changes in patients undergoing EVAR procedures [4,5,6,7,8,9,10,12]. The manipulation of guidewires and catheters in the vessels may enhance the intraoperative injury of the vascular endothelium, leading to increased thrombin generation and activity [10,13,14]. Furthermore, contrast media can be linked with platelet activation and endothelial cell injury [10,15,16]. Moving on to intramural sac thrombus, in contrast to OS, the intramural sac thrombus is not removed during an EVAR procedure. It has been suggested that the remanence of an intramural thrombus after EVAR could serve as a possible mechanism for persistent (up to 12 months) hypercoagulability, when compared to OS [10,13,17]. Normally, the exclusion of the aneurysm sac from the circulation leads to complete sac thrombosis with subsequent platelet consumption, increased coagulation, and fibrinolysis activation [10]. In type II endoleak, only partial sac thrombosis occurs; the aneurysm thrombus remains in situ and in contact with the systemic circulation. However, notably, even in the absence of a clinically significant endoleak, the thrombus could still remain in contact with the systemic circulation through the small feeding lumbar arteries or the mesenteric circulation [10,13,17].

### 1.2. Aims

To our knowledge, no specific analysis of coagulation changes or platelet activation after complex EVAR has been performed to date. Considering the high complexity of the repair and the longer stent graft in complex EVAR, we decided to assess the hypothesis that the complex EVAR of para-renal and thoraco-abdominal aortic aneurysms might induce a more severe coagulation response along with a more prominent platelet activation.

### 1.3. Objectives

(1)To evaluate the early (postoperative day one) and late (postoperative day 3 or 4) effects of complex EVAR of para-renal and thoraco-abdominal aortic aneurysms on coagulation, with respect to von Willebrand factor (vWF), factors VIII and XI, D-dimers, fibrinogen, Adamts-13 levels, and platelet activation, in patients undergoing complex para-renal and thoraco-abdominal aortic aneurysm repair (primary endpoint);(2)To record the incidence of myocardial injury after non-cardiac surgery (MINS), major adverse cardiovascular events after non-cardiac surgery (MACE), acute kidney injury (AKI), post-implantation syndrome (PIS), and death from any cause during hospitalization;(3)To record the incidence of MACE, implant failure, or death from any cause at 30 days and 3, 6, and 12 months postoperatively.

## 2. Materials and Methods

### 2.1. Experimental Design

This is a prospective observational study that will be conducted at a single tertiary/referral University Hospital using the STROBE guidelines (Strengthening the Reporting of Observational Studies in Epidemiology) [18].

### 2.2. Study Setting

This prospective observational study will be conducted in a tertiary institution, i.e., the Larissa University Hospital (UHL). The study plan and data collection are summarized in Figure 1.

### 2.3. Study Schedule

Preoperatively and before induction to general anesthesia, the preoperative data, including demographics (age, gender, body mass index), American Society of Anesthesiologists physical status (ASA PS), any comorbidities and administrated drug therapy, smoking status and alcohol intake, the size of aneurysm, the type of graft used, and baseline liver and renal function will be recorded. In addition, a complete blood count, conventional coagulation tests, kidney and liver function tests, vWF, factors VIII and XI, D-dimers, fibrinogen, Adamts-13, platelet activation (multiplate), and high-sensitivity troponin will be obtained. The anti-Xa value will also be determined in order to rule out an anticoagulant effect on the laboratory tests.

At the first postoperative day, the duration of surgery and the possible occurrence of MINS, MACE, AKI, and PIS will be recorded, while a complete blood count, conventional coagulation tests, kidney and liver function tests, vWF, factors VIII and XI, D-dimers, fibrinogen, Adamts-13, platelet activation (multiplate), and high-sensitivity troponin will be obtained. The anti-Xa value will also be determined in order to rule out an anticoagulant effect on the laboratory tests.

At the 3rd or 4th postoperative day, based on the date of discharge, the length of hospitalization, the number of transfusion units, and the possible occurrence of MINS, MACE, AKI, and PIS will be recorded. In addition, a complete blood count, conventional coagulation tests, kidney and liver function tests, vWF, factors VIII and XI, D-dimers, fibrinogen, Adamts-13, platelet activation (multiplate), and high-sensitivity troponin will be obtained from a peripheral vein. The anti-Xa value, correlated to the weight and the dose of the anticoagulant, is also determined in order to rule out an anticoagulant effect on the laboratory tests.

At 1, 3, 6, and 12 months postoperatively, MACE, implant failure (including secondary sac rupture, graft explantation, type 1 or 3 endoleak, or major mitigation of the stent grafts), and death from any cause will be recorded. The study plan and data collection are summarized in Figure 1.

### 2.4. Participants

Consecutive patients with para-renal and thoraco-abdominal aortic aneurysms undergoing complex EVAR will be included. All patients will be followed up for 12 months. In general, patients will be treated according to the guidelines of the European Society for Vascular Surgery (ESVS) [19].

### 2.5. Eligibility Criteria

Consecutive adult patients, 18 years or older, with para-renal and thoraco-abdominal aortic aneurysms undergoing complex EVAR will be included.

Patients that refuse to participate, those who have undergone any prior surgery within 3 months, those with history of inherited or acquired bleeding disorder, those with inherited or acquired platelet dysfunction, those with factor V Leiden or any type of thrombophilia, antiphospholipid syndrome, protein C or S deficiency, or patients with an active malignancy or a connective tissue or rheumatoid disease and patients classified as ASA PS > 3 will be excluded. Inclusion and exclusion criteria are presented in Table 1 and Table 2.

### 2.6. Standard Perioperative Care

Perioperative care will be provided in accordance with institutional guidelines and the updated Clinical Practice Guidelines on the Management of Abdominal Aorto-iliac Artery Aneurysms [19]. All patients will be treated by the same surgical and anesthesiologic team in a fully equipped operating theatre under general anesthesia. Intravenous induction to general anesthesia will be achieved with propofol and maintenance with desflurane and dexmedetomidine. In addition to standard monitoring (electrocardiogram, blood pressure, and pulse oximeter), depth of anesthesia, invasive blood pressure, and goal-directed fluid-therapy monitoring will be applied. Every effort will be made to follow the selection criteria recommended by the stent graft manufacturer. However, the final decision will be made by the treating surgeon.

Preoperatively, patients will be treated with 100 mg of aspirin once daily for at least 5 days. If the patient has been treated with clopidogrel, this will be switched to aspirin preoperatively for 10 days [20]. Postoperatively, patients will receive 100 mg of aspirin if there is no bleeding and 75 mg of clopidogrel if there is no neurological dysfunction due to spinal ischemia and dual antiplatelet therapy (DAPT, aspirin 100 mg and clopidogrel 75 mg) from the next day. If the patient has been treated with anticoagulants, these will be discontinued preoperatively in accordance with the ACCP guidelines and resumed on postoperative day 1 or 2, depending on hemostasis [20]. In this case, patients will be treated preoperatively with aspirin 100 mg once daily for 5 days, and aspirin will be continued postoperatively.

Systemic heparinization of the patient will be achieved with 5000 units of unfractionated heparin intraoperatively. One hour after the first administration of heparin, and every 30 min thereafter, the activated clotting time (ACT) will be measured. The intraoperative ACT target is set at 200–300 s.

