### 2.8. Data Collection

Most of the data will be obtained from the routine admission documents and the electronic patient file. They will be recorded in a password-protected spreadsheet. Basic data collection will include demographics (age, gender, body mass index), ASA physical status, any comorbidities and administrated drug therapy, smoking status and alcohol intake, the size of aneurysm, the type of graft, liver and renal function, the duration of surgery, the length of hospitalization, the number of transfusion units, and the possible occurrence of MINS, MACE, AKI, and PIS. The basic data that will be collected are presented in Table 3.

As far as the laboratory values are concerned, the following parameters will be determined: vWF, factors VIII and XI, D-dimers, fibrinogen, Adamts-13, platelet activation (multiplate), and high-sensitivity troponin. All samples will be taken by puncturing a peripheral vein. The blood samples will be taken at three points in time: preoperatively before induction of general anesthesia, early postoperatively (1st postoperative day), and late postoperatively (3rd–4th postoperative day). The anti-Xa value, correlated to the weight and the dose of the anticoagulant, will also be determined in order to rule out an anticoagulant effect on the laboratory tests. The additional laboratory values that will be collected are presented in Table 4.

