## Figures and Tables

**Figure 1 jcm-14-03105-f001:**
[figure not shown]
Study timeline.

**Table 1 jcm-14-03105-t001:** Inclusion Criteria.

Inclusion Criteria
Age > 18 years
Consecutive patients undergoing complex thoraco-abdominal aortic aneurysm repair in UHL

**Table 2 jcm-14-03105-t002:** Exclusion Criteria.

Exclusion Criteria
Refuse to participate
Prior surgery within 3 months
History of inherited or acquired bleeding disorder
History of inherited or acquired platelet dysfunction
Patients with factor V Leiden or any type of thrombophilia
Patients with antiphospholipid syndrome
Patients with protein C or S deficiency
Patients with connective tissue or rheumatoid disease
Patients with an active malignancy
ASA PS > 3

**Table 3 jcm-14-03105-t003:** Basic Data Collection.

Basic Data Collection	
Demographics: age, gender, body mass index	MINS
ASA PS	MACE
Comorbidities and administrated drug therapy	AKI
Lifestyle: smoking status, alcohol intake	PIS
Size of aneurysm	Duration of surgery
Type of graft	Length of hospitalization
Liver and renal function	Transfusion units

MINS: myocardial injury after non-cardiac surgery, MACE: major adverse cardiovascular events after non-cardiac surgery, AKI: acute kidney injury, PIS: post-implantation syndrome (PIS).

**Table 4 jcm-14-03105-t004:** Laboratory values.

Laboratory Values	
vWF	Factor VIII
Factor XI	D-dimers
Fibrinogen	Adamts-13
Platelet function (multiplate R)	Anti-Xa

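### The default antiplatelet regimen changes at the time of surgery, so the change in Multiplate, one of seven primary components, cannot be attributed to complex EVAR alone

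*Protocol article*

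**What the plan says.** Sections 1.3 and 2.7 of the Protocol article list seven primary components: vWF, factors VIII and XI, D-dimers, fibrinogen, Adamts-13 and platelet activation by Multiplate. Each is sampled before induction, on postoperative day 1 and on day 3–4. Section 3.1 states that there is one arm, and section 3.2 compares the time points by repeated-measures ANOVA or a nonparametric counterpart.

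Section 2.6 sets the drug background.

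- **Before surgery:** "Preoperatively, patients will be treated with 100 mg of aspirin once daily for at least 5 days". For prior clopidogrel users, "If the patient has been treated with clopidogrel, this will be switched to aspirin preoperatively for 10 days".
- **After surgery:** aspirin depends on the absence of bleeding. Clopidogrel carries its own condition: "75 mg of clopidogrel if there is no neurological dysfunction due to spinal ischemia". The same sentence then describes the combined regimen as "dual antiplatelet therapy (DAPT, aspirin 100 mg and clopidogrel 75 mg) from the next day".
- **Previously anticoagulated patients:** the anticoagulant is stopped and then "resumed on postoperative day 1 or 2, depending on hemostasis". For their antiplatelet treatment, "In this case, patients will be treated preoperatively with aspirin 100 mg once daily for 5 days, and aspirin will be continued postoperatively".

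The laboratory check described for drug effects is anti-Xa, which "will also be determined in order to rule out an anticoagulant effect on the laboratory tests" (section 2.8; sections 2.3 and 2.7 say the same). The limitations in section 6 name the single centre, the single arm and the choice of laboratory values. They do not name the antiplatelet change.

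**The concern.** The baseline Multiplate reading is taken on aspirin without clopidogrel. By default, later readings are taken after clopidogrel has been added. The regimen and the exposure under study change together, and there is no control group in which one changes without the other.

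Section 1.2 hypothesises a more prominent platelet activation. Clopidogrel is an antiplatelet drug and would be expected to push a platelet aggregation reading the other way. A true procedure-related rise could be masked, or a drug-related fall could be reported as an effect of complex EVAR. The investigators already accept that drugs can distort the assays, since they measure anti-Xa for that purpose, but anti-Xa says nothing about antiplatelet drugs.

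The order of dose and draw, and the drugs on board at each draw, must be captured when the sample is taken. Later analysis cannot recover them.

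**Working it through.** **1. Drug state at each draw (section 2.6 against the sampling times in section 2.7).**

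| Draw | Default patient | Previously anticoagulated patient |
|---|---|---|
| Before induction | Aspirin; clopidogrel users switched | Aspirin; anticoagulant stopped |
| Day 1 | Uncertain | Aspirin; anticoagulant possibly resumed |
| Day 3–4 | Aspirin plus clopidogrel, unless bleeding or spinal ischaemia intervenes | Aspirin plus resumed anticoagulant |

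Day 1 is uncertain for two reasons. The order of the draw and that day's dose is not fixed. The sentence on postoperative treatment can also be read either as clopidogrel after surgery followed by the combination next day, or as both starting next day.

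**2. The plan's own sample size.** Inputs from section 3.1: f = 0.25, alpha = 0.05, power 95%, three measurements, N = 58 (65 after dropout allowance). The formula for a one-group within-factor design uses a noncentral F with λ = f²·n·m·ε/(1−ρ), df1 = (m−1)ε, df2 = (n−1)(m−1)ε and m = 3. The article gives neither the correlation ρ nor the sphericity factor ε.

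- ρ = 0.5, ε = 1: N = 43
- ρ = 0.32, ε = 1: N = 58
- ρ = 0.5, ε = 0.65: N = 59
- ρ = 0.6, ε = 0.5: N = 58

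So 58 is attainable but cannot be confirmed from the stated inputs. The present point does not depend on it.

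**3. The design effect in SD units.** f is the square root of the mean squared deviation of the three means, divided by the SD.

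- One draw differs by d: f = d·√2/3 = 0.471d, so d = 0.25/0.471 = 0.53 SD.
- Linear trend with end-to-end difference d: f = d/√6 = 0.408d, so d = 0.25/0.408 = 0.61 SD.

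**4. The possible drug shift (assumed).** Average shift = drug effect × share treated. The document gives neither figure. Assume 0.5–1.5 SD and 70–90%.

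- Low end: 0.5 × 0.7 = 0.35 SD, so f = 0.471 × 0.35 = 0.165.
- High end: 1.5 × 0.9 = 1.35 SD, so f = 0.471 × 1.35 = 0.636.

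The range starts below 0.53–0.61 SD and ends well above it.

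**5. What a pure drug shift would do.** Take a zero procedure effect, n = 58 and ε = 1, with the shift on day 3–4 only or equally on both postoperative draws (f is the same). The probability that the time effect is significant is:

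| Average shift (assumed) | f | ρ = 0.3 | ρ = 0.5 |
|---|---|---|---|
| 0.2 SD | 0.094 | 0.24 | 0.32 |
| 0.3 SD | 0.141 | 0.49 | 0.64 |
| 0.5 SD | 0.236 | 0.92 | 0.98 |
| 0.8 SD | 0.377 | about 1.00 | about 1.00 |

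A 0.5 SD average shift alone gives nearly the design effect. The table treats the shift as common to all patients, so it is an illustration and not a prediction.

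**The case against.** Several counter-arguments are fair.

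- **Drug data are not limited to baseline.** Section 2.3 lists drug therapy under preoperative data, and a reader might infer that it is recorded only then. Section 2.8 and Table 3 list it with no time limit, and anti-Xa is related to the anticoagulant dose. That inference is not supported. Even so, nothing stated ties antiplatelet exposure to each draw.
- **Exposure is not universal.** A reader might take every day 3–4 sample to be on dual therapy. The exceptions for bleeding, spinal ischaemia and prior anticoagulation rule that out. They also make exposure depend on clinical course.
- **The size is assumed.** One might conclude that the artefact is at least as large as the effect sought, or that any fall is entirely pharmacological. The document supports neither: no agonist is named, and the low end of the assumed range is below the design effect.
- **The clotting assays.** Clopidogrel does not by itself put the coagulation-factor components in doubt. Resumed anticoagulants concern only a subgroup, and conventional coagulation tests are taken at all three draws as well as anti-Xa.
- **An article condenses.** Dose-time fields and draw rules may stand in a fuller document, so their absence here is not the finding. The finding is that the stated regimen change coincides with the procedure in a stated single-arm comparison over time.
- **Regression is planned (section 3.2).** With one arm and a change in most patients at the time of surgery, adjustment cannot cleanly separate drug from procedure.

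**Conclusion.** The point holds for the platelet component. As planned, a change in Multiplate from baseline to day 3–4 reflects the procedure together with a change of antiplatelet regimen in most patients, and anti-Xa cannot tell them apart. The same may apply at day 1, where the text leaves exposure open.

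The size cannot be derived from the document. Under the stated assumptions it is 0.35–1.35 SD, against 0.53–0.61 SD for f = 0.25. It could therefore be somewhat smaller than the effect the study is sized for, or well above it. No stated figure is wrong and no new sample size follows. The other six primary components are not affected by the clopidogrel change on this argument. It should be settled before samples are drawn.

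**What to change.** No change of treatment is proposed.

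1. Record each antiplatelet and anticoagulant drug, with the time of last dose, at all three draws.
2. Take the day-1 research sample before that day's antiplatelet dose. The investigators should reconcile the sentence in section 2.6 on when postoperative clopidogrel starts; until then, a pre-dose draw does not guarantee a clopidogrel-free sample.
3. Report postoperative Multiplate by the regimen at the draw. Label day 3–4 as procedure plus antiplatelet regimen, not as an effect of complex EVAR, and add this to section 6.
4. As a sensitivity analysis only, repeat the clotting-factor comparison without draws that show measurable anti-Xa or resumed oral anticoagulation, and state that this selects on events after baseline.

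Two other steps may suggest themselves, and I would not take them. Adjusting for the postoperative platelet count may remove part of the procedure effect, because section 1.1 says EVAR itself lowers the count. Restricting the primary contrast to patients still on aspirin alone could select by clinical course.

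The cost is a few data fields per draw, a draw-time rule, a little more analysis, and a weaker conclusion from the day 3–4 platelet result.
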